## Abstract

**Background:**

Perinatal mental health problems affect up to one in five women worldwide. Mental health problems in the perinatal period are a particular challenge in low- and middle-income countries (LMICs) where they can be at least twice as frequent as in higher-income countries. It is thus of high priority to develop new low-cost, low-resource, non-stigmatising and culturally appropriate approaches to reduce symptoms of anxiety and depression perinatally, for the benefit of both mother and child. Music-centred approaches may be particularly useful in The Gambia since a range of musical practices that specifically engage pregnant women and new mothers already exist.

**Methods:**

This protocol is for a study to examine the feasibility of undertaking a stepped wedge trial to test how a Community Health Intervention through Musical Engagement (CHIME) could be beneficial in alleviating perinatal mental distress in The Gambia. In this study, we plan to recruit 120 pregnant women (*n* = 60 intervention, *n* = 60 control) at four antenatal clinics over two 6-week stepped sequences. Women in the intervention will participate in weekly group-singing sessions, led by local Kanyeleng singing groups, for 6 weeks. The control group will receive standard care. We will assess symptoms of anxiety and depression using the Edinburgh Postnatal Depression Scale (EPDS) and the Self-Reporting Questionnaire (SRQ-20). The feasibility of the design will be assessed through recruitment, retention and attrition rates of participants, clinics' adherence to the schedule and completeness of data by site. Qualitative interviews and video and audio recordings will be used to evaluate the acceptability of the intervention.

**Discussion:**

This feasibility trial will allow us to determine whether a larger trial with the same intervention and target group is feasible and acceptable in The Gambia.

**Trial registration:**

Retrospectively registered (24/01/2019) with Pan African Clinical Trials Registry (PACTR): PACTR201901917619299.

## Background

Perinatal mental health problems affect up to one in five women worldwide [1, 2]. Stress, anxiety and depression in pregnancy affect not only the mother but can also have long-term adverse effects on her child via biological mechanisms in utero [3]. Along with the impact on the mother and her developing infant, antenatal depression and anxiety are the most common predictors of postnatal depression [4, 5]. Postnatal depression can reduce her ability to provide sensitive and responsive caregiving that can potentially impair child development [6]. Mental health problems in the perinatal period are a particular challenge in low- and middle-income countries (LMICs) where they can be at least twice as frequent as in higher-income countries [1]. Our geographical context for this work will be The Gambia, in West Africa, where mental health services are minimal, services for perinatal mental health are non-existent and high levels of stigma associated with mental health issues, as well as specific local attitudes and beliefs, impede recognition and prevent help-seeking behaviour. It is thus of high priority to develop new low-cost, low-resource, non-stigmatising and culturally appropriate approaches to reduce symptoms of anxiety and depression perinatally, for the benefit of both the mother and child.

The current project will test the hypothesis that the creative arts—in particular group-singing—will show special promise in alleviating perinatal mental distress in The Gambia. In high-income countries, such as the UK and the USA, singing in groups has been shown to be a powerful modulator of mood and emotion, evoking positive effects on mental health, well-being and social affiliation [7] via mechanisms involving synchrony and entrainment [8], the saliency of relational communicative features in musical interaction [9] and significant effects on the endocrine system [10]. In addition, the mother’s voice is a key channel through which meaningful, sensitive and contingent interactions between the caregiver and infant can take place [11]. Recent studies have found that music and its use specifically during the perinatal period can reduce women’s stress levels and depressive symptoms and increase women’s attachment to their infant [12–15]. Music-centred approaches may be particularly fruitful in The Gambia as there are already a range of musical practices that specifically engage pregnant women and new mothers [16]. For instance, infant naming ceremonies occur 7 days after birth and are musical celebrations to recognise the new mother and her family [16]. Performances by Kanyeleng groups are closely associated with pregnancy and motherhood and are important in health communication [17]. These pre-existing cultural and creative practices provide an excellent context from which to explore, co-design and ultimately evaluate culturally situated, music-centred interventions that aim to reduce symptoms of anxiety and depression perinatally and facilitate mother-infant caregiving.

### Study aims

This is a feasibility study which aims to inform the design of a larger trial to investigate a Community Health Intervention through Musical Engagement (CHIME) to help reduce symptoms of anxiety and depression in pregnant women compared to standard care. This article describes the trial protocol (version 1.0, 11/11/18). The protocol was prepared in accordance with the Standard Protocol Items: Recommendations for Interventional Trials (SPIRIT) guidance. The trial SPIRIT checklist can be viewed in Additional file 1.

### Objectives

Our primary objective is to test (a) the feasibility of delivering a group-singing intervention to a sample of pregnant women in The Gambia using a stepped wedge design and (b) the feasibility of using standardised tools to measure the impact of this intervention on anxiety and depression symptoms, before and after the intervention.

This objective can be broken down into five specific feasibility objectives:
To obtain demographic information on the eligible populationTo determine if our measurement tools, the Edinburgh Postnatal Depression Scale (EPDS) and the Self-Reporting Questionnaire (SRQ-20), are useableTo determine if the intervention is deliverableTo determine if the stepped wedge trial design is deliverable and obtain information that will inform the definitive study. Specifically to:
Assess recruitment and acceptability of randomising clinicsAssess the recruitment rate of women to control and intervention groupsAssess participants’ adherence to the intervention group and follow-up in both armsTest the feasibility of data collectionTo determine if this type of intervention is culturally appropriate and well received by the community and health workers.

## Methods/design

We will be testing the feasibility of a stepped wedge cluster design, which differs from a parallel arm cluster design in that all clinics involved in the study receive the intervention [18]. Advantages over a parallel arm cluster trial include the requirement of a smaller sample size due to the availability of a within group comparison and prevention of potential disappointment for health clinics who are not randomised into the intervention.

### Study setting

This multi-site study will recruit from four antenatal clinics in western Gambia.

### Study population

All participants will be Mandinka or Wolof Gambian women who are pregnant.

Inclusion criteria
Pregnant (14–24 weeks gestation)Speak Wolof or Mandinka fluently

Exclusion criteria
At least one previous late term miscarriageCurrent psychosis or history of psychosis

Withdrawal criteria

If the participant develops any serious medical condition or the participant’s mental health significantly declines (as assessed by the care team), and the care team deem it necessary, then she may be withdrawn from the study.

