### Outcome measurements

Two local research assistants (RAs) will collect all measures orally as there is a high rate of illiteracy among the target population. All scales have been translated into Mandinka and Wolof. The translation method used was based on suggestions by the World Health Organisation, Hanlon et al. [19] and Cox, Holden and Henshaw [20]. First, the scales were translated into Mandinka and Wolof. An expert panel discussion then refined the translation before back translating it into English. The expert panel came together once more to resolve any remaining issues before finalising the translation.

Two questionnaires will measure antenatal anxiety and depression symptoms. The Edinburgh Postnatal Depression Scale (EPDS) [21] is a ten-item scale that was developed to screen for postnatal depression. It has subsequently been validated to be used during pregnancy [22]. This measurement tool has been used and validated in other African contexts; however, there is no avaliable validated version of the EPDS in Mandinka or Wolof even though it has been used in The Gambia before [23]. The Self-report Questionnaire (SRQ-20) [24] is a 20-item scale developed by the World Health Organization to measure anxiety and depression symptoms in a variety of cultural contexts. It has been used in many different African contexts such as Ethiopia [19], South Africa [25] and Rwanda [26] and as a way to measure perinatal mental health [23]. However, the SRQ-20 has never been used in the Gambian context nor has it been translated into Wolof or Mandinka.

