### Sample size

As this is a feasibility study, it is not designed to assess the efficacy of the intervention, although pilot data on this will be collected. We will evaluate the feasibility of study design, data collection and whether the intervention is deliverable and acceptable to the participants. In the study, we will gather information to be used in the design of the future definitive study including an estimate of the standard deviation of potential primary outcomes to inform the sample size. We aim to collect data from a total of 120 pregnant women, 60 in the control condition and 60 in the intervention condition [27]. This number will be sufficient to provide estimates of binary feasibility outcomes with precision of at least ± 9 percentage points for the 95% confidence interval.

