### Analysis

All data will be entered into a database by an RA and verified by the second RA using double data entry to ensure data quality. As this is a feasibility study, we will examine missing data as an outcome.

Descriptive statistics will be summarised to understand the demographic variables relating to the recruited population. Descriptive statistics and plots will be used to assess the distribution of the measurement tools, repeated at baseline and follow-up and by each arm. We will also examine the distributions of scores in the different language groups to see to what extent item scores and overall distributions differ or are similar. Correlations between our two measurement tools will be calculated.

To determine if the intervention is deliverable, we will record the number of sessions that the Kanyeleng groups delivered, aiming to deliver two thirds of the sessions, and the duration of each session, aiming to last between 45 and 75 min. We will also perform a qualitative evaluation, using the video and audio recordings, to determine intervention fidelity at the four sites. Both RAs will watch the video and audio recordings of the first and fourth group-singing sessions at each clinic and complete a checklist to determine if all the necessary elements—as outlined in the training workshops—were included in the intervention. Reliability of the fidelity measure will be ascertained by measuring inter-rater consistency.

We will also calculate the proportion of clinics approached that consented, aiming to reach over 50% recruitment rate, and record any scheduling problems in keeping with the stepped wedge timeline. Recruitment, adherence and completeness of data will be calculated for both groups. We aim to achieve a 60% recruitment rate and no more than 30% attrition in both arms. To determine if the intervention was culturally appropriate and well received by the community and health workers, we will collect qualitative data from post-intervention interviews and perform a thematic analysis.

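### Withdrawal for declining mental health ends study participation, not only singing, so week-7 and week-11 EPDS and SRQ-20 scores go missing for a reason related to the outcome

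*Protocol article*

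**What the plan says.** The withdrawal criteria (Protocol article, Study population) cover a serious medical condition and, in the same sentence, a woman whose "mental health significantly declines (as assessed by the care team), and the care team deem it necessary, then she may be withdrawn from the study". This point concerns the mental health route only. The criterion is not restricted to the singing group; control women, who receive standard care alone, fall under it too.

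Under Outcome measurements, "Two questionnaires will measure antenatal anxiety and depression symptoms": the EPDS and the SRQ-20. Trial schedule places data collection at weeks 1, 7 and 11.

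Three planned outputs depend on those data:

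- Sample size promises "an estimate of the standard deviation of potential primary outcomes to inform the sample size" of the definitive study.
- Analysis describes score distributions at baseline and follow-up by arm, and examines missing data as an outcome.
- Analysis sets a target of "no more than 30% attrition in both arms".

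Assessment and management of risk provides that a woman with a high score, or who is struggling, is referred to the community mental health team. It does not mention withdrawal.

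**The concern.** Leaving the study is tied to the construct that the study measures. A woman withdrawn after baseline for worsening mental health has no later scores, and those scores would tend to have been high. The missingness is therefore informative, and describing only the observed scores does not correct for it.

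The criterion does not separate stopping the singing sessions from stopping data collection. For a control woman there are no sessions to stop, so statistically the withdrawal only ends her assessments.

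Three deliverables are affected: the post-baseline score distributions, any SD for the definitive trial taken from week 7 or week 11, and the attrition figure. The last would combine women removed by the care team with women who chose to leave. Only the latter say much about whether the study is acceptable to participants.

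**Working it through.** **The plan's own figure.** Sample size states "precision of at least ± 9 percentage points for the 95% confidence interval" for 120 women. At the worst case p = 0.5, 1.96 × √(0.25/120) = 8.95 points. The figure reproduces and is not in dispute here.

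**Inputs.** 60 women per arm (Sample size) and the 30% attrition limit (Analysis). The document gives no withdrawal rate and no baseline-to-follow-up correlation. Assumptions: a fraction q = 2%, 5% or 10% is withdrawn; scores are normal with SD 1 and the same variance at both times; the correlation ρ is 0.5 or 0.7.

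**Case A: the women who worsen most are removed.** This is closer to the rule, which speaks of decline. Let z be the upper-q normal point, λ = φ(z)/(1 − q) and v = 1 − zλ − λ². The squared correlation between the follow-up score and the change from baseline is (1 − ρ)/2, that is 0.25 for ρ = 0.5 and 0.15 for ρ = 0.7. Among the women who remain:

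- mean shift = −λ√((1 − ρ)/2)
- variance = 1 − ((1 − ρ)/2)(1 − v)

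| q | λ | v | ρ | Mean shift (SD) | Variance ratio | SD ratio |
|---|---|---|---|---|---|---|
| 2% | 0.049 | 0.896 | 0.5 | −0.025 | 0.974 | 0.987 |
| 2% | 0.049 | 0.896 | 0.7 | −0.019 | 0.984 | 0.992 |
| 5% | 0.109 | 0.810 | 0.5 | −0.054 | 0.952 | 0.976 |
| 5% | 0.109 | 0.810 | 0.7 | −0.042 | 0.971 | 0.986 |
| 10% | 0.195 | 0.712 | 0.5 | −0.097 | 0.928 | 0.963 |
| 10% | 0.195 | 0.712 | 0.7 | −0.076 | 0.957 | 0.978 |

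A simulation of two million women agrees to within 0.002 on the variance ratio; for the mildest case it gives 0.986. Sample size for a comparison of means is proportional to SD², so the shortfall is 1 minus the variance ratio: about 1% to 7%.

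**Case B: the highest scorers are removed.** This is the severe case. The mean shift is −λ and the variance is v.

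| q | Mean shift (SD) | SD ratio | Sample size too small by |
|---|---|---|---|
| 2% | −0.05 | 0.95 | 10% |
| 5% | −0.11 | 0.90 | 19% |
| 10% | −0.20 | 0.84 | 29% |

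Case B is the upper end for normal scores. If scores were strongly right-skewed (a gamma distribution with shape 2 was tried), hard removal of the top 2%, 5% or 10% would leave an SD ratio of 0.87, 0.77 or 0.67. The direction was the same in every scenario: lower mean, smaller SD.

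**Attrition.** One woman is 1/60 = 1.7 points of an arm. The 30% limit allows 0.30 × 60 = 18 losses. Three care-team withdrawals use 5 points; six use 10 points, a third of the allowance.

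**The case against.** The strongest reply is that the rule is narrow. It requires a significant decline, assessed by the care team, and their judgement that withdrawal is necessary; even then a woman only may be withdrawn. Few women may be affected. This stands, and it limits the size.

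Several stronger readings are tempting but unsupported:

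- **A reader might infer that the questionnaire score itself decides who is measured.** No EPDS or SRQ-20 cut-off triggers withdrawal, and the only stated consequence of a high score is referral.
- **A reader might infer that the SD for the definitive trial must be too small.** Sample size does not say which time point supplies it, and week-1 scores precede any such withdrawal. Case A's bias of about 1–4% in the SD also lies inside the sampling error of an SD, roughly 1/√(2(n − 1)): 6.5% at n = 120, and 7.8% at n = 84 (30% attrition). Sampling error does not share the bias's fixed direction, however, and Case B's bias reaches 16%.
- **A reader might infer that data already collected are dropped.** Nothing says so.
- **A reader might infer that withdrawal will differ by arm.** Researchers and participants are unblinded, and intervention women have extra clinic contacts, so this is possible. But the document does not say what the care team knows, and it says that women throughout the study are monitored.

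It is also fair to say that withdrawal spares a distressed woman further sensitive questions, and that a breakdown of losses by reason may be left to a fuller document. The first is a reason to keep an exception. The second does not change the stated rule, which ends study participation.

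**Conclusion.** The point holds as a moderate one: the criterion should be changed, but it does not undermine the study. Followed as written, it makes week-7 and week-11 scores informatively missing in either arm, lowers the post-baseline mean and SD, and adds to the figure judged against the 30% limit.

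Its size cannot be determined from the document. With 2–10% of women withdrawn, the SD is about 0.96–0.99 of true and a sample size built on it about 1–7% too small if those who worsen most leave (ρ of 0.5–0.7 and normal scores assumed). If the highest scorers leave, the figures are 0.95–0.84 and about 10–29%. The first range fits the wording better; the second should be read as the severe end and not as an expected value.

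A reader might go on to infer an invalid treatment comparison. The study states that it is not designed to assess efficacy, so no hypothesis test is at risk; only the pilot outcome data and the feasibility figures are.

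**What to change.** Leave every decision on care and on attending sessions with the care team. Add to the withdrawal criteria that stopping the sessions does not by itself end data collection: the week-7 and week-11 EPDS and SRQ-20 are still sought, in both arms, unless the woman withdraws consent to data collection or the care team judges the interview unsuitable.

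In Analysis, report care-team withdrawals by arm, separately from voluntary attrition, and show the 30% criterion with that split. In Sample size, base the SD for the definitive trial on baseline as well as follow-up scores.

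The cost is a sentence in each of the three sections and one category on the case report form. The downside is a few sensitive follow-up interviews, conducted by research assistants who are already trained psychiatric nurses. Because the exception for unsuitable interviews again concerns the most unwell women, some outcome-related missingness will remain; it will at least be counted.

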### Intervention

The intervention will be delivered on the community level, meaning that it will include women with a range of anxiety and depression symptoms. Our primary aim is to reduce symptoms in those experiencing them (whether these are at a high level or a medium or low level). We anticipate this may also help to reduce their symptoms into the postnatal period. By including those with low and high levels of symptoms, rather than screening and including only those with high levels of symptoms, we will aim to avoid stigma and increase acceptability.

The intervention has been developed following focus groups with various stakeholders including health professionals (midwives and community birth companions), pregnant women and musicians (griots and Kanyeleng groups).

Four groups of 20 women between 14 and 24 weeks gestation will attend six 60-min group-singing sessions at their local antenatal clinic. This will take place in the morning as this is the time deemed to best suit the majority of women and clinics. Local Kanyeleng groups who specialise in musical practices to support women’s health will lead the sessions. The content of the six sessions will be co-designed with the Kanyeleng groups via two extended workshops with the research team. All sessions will begin with a welcome song and end with a closing song. Some of the songs used during the main body of the session will cover topics including the (a) importance of the singing group in supporting each other, (b) importance of other positive relationships in their lives, (c) resilience to challenges and empowerment and (d) importance of being open, removing stigma to discuss challenges. One lullaby will be introduced at each session. Kanyeleng leaders will also be encouraged to ensure that all the women feel comfortable and are participating when they can.

The nature of the intervention will necessarily vary somewhat across the four settings, especially as Wolof speaking groups and Mandinka groups have different and distinct cultural beliefs, practices and language. By using the Kanyeleng groups local to each of the four clinics involved, the sessions will be contextually appropriate, while the workshop with all four Kanyeleng groups before the intervention begins will ensure that the overarching goals, content and approach to session delivery are broadly standardised.

Over the course of the 6-week intervention period, a research assistant will observe and video and audio record two singing sessions (the first and the fourth sessions) from each of the four clinics to ascertain, using a checklist, the extent to which the sessions conform to our articulated goals. A community health nurse at each clinic will be engaged to take attendance data and report any issues of concern to the research team.

The control group will consist of four groups of 20 women between 14 and 24 weeks gestation from the same four clinics. These women will receive only standard care without any additional intervention.

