### Trial schedule

This trial design involves a sequential crossover of clusters whereby each cluster (antenatal clinic) receives the control condition followed by the intervention condition. The four chosen clinics will be randomised to two sequences of a 12-week phase. A separate cohort of participants will be recruited to the control group and the intervention (singing) group. Each cohort will be recruited around 4–6 months into their pregnancy. The 12-week phase for both the control and intervention cohort will include data collection at week 1 (“baseline”) and week 7 (“post”) after either group-singing (intervention) or standard care (control) as well as at week 11 (“follow-up”), 4 weeks after the intervention finished. Contamination will be avoided by having data for the control group collected before the intervention groups start at each clinic. See Fig. 1 for a schematic for the study.

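### The protocol gives two incompatible sample sizes: groups of 20 at four clinics make 160 women (80 per arm), while the abstract and sample-size section give 120 (60 per arm)

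*Protocol article*

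**What the plan says.** Four places in the protocol article bear on the number of women.

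- **Intervention, on the singing arm:** "Four groups of 20 women between 14 and 24 weeks gestation will attend six 60-min group-singing sessions at their local antenatal clinic".
- **Intervention, on the control arm:** "The control group will consist of four groups of 20 women between 14 and 24 weeks gestation from the same four clinics".
- **Abstract, Methods:** "we plan to recruit 120 pregnant women (*n* = 60 intervention, *n* = 60 control) at four antenatal clinics".
- **Sample size:** "We aim to collect data from a total of 120 pregnant women, 60 in the control condition and 60 in the intervention condition". The same section ties this number to a "precision of at least ± 9 percentage points for the 95% confidence interval" for binary feasibility outcomes.

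Two further statements fix how the counts add up. Study setting says "This multi-site study will recruit from four antenatal clinics in western Gambia". Trial schedule says "A separate cohort of participants will be recruited to the control group and the intervention (singing) group", so no woman is counted in both conditions.

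The Analysis section sets feasibility targets of a 60% recruitment rate and attrition of at most 30% in each arm. It does not connect either figure to the sample size.

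**The concern.** The group description and the sample-size statement cannot both be the recruitment plan. If each of four clinics fills a singing group of 20 and a control group of 20, the study enrols 160 women. If it enrols 120, the groups average 15.

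Three things depend on which number is meant:

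- **The planned N.** A reader cannot tell from the article how many women the study intends to enrol. A final enrolment of 120 is either exactly as planned or 40 short.
- **The size of the singing group.** The intervention is delivered to a group, and the topics listed for the songs include the group's role in mutual support. Twenty women or an average of fifteen is therefore part of what is being tested for deliverability.
- **The workload.** Two research assistants collect every measure orally, on a fixed stepped timetable. The number of women to be approached, consented and interviewed changes by a third.

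**Working it through.** **Inputs, all from the protocol article**

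- Clinics: 4 (Study setting).
- Group size: 20 in each condition (Intervention).
- Cohorts: separate for control and intervention (Trial schedule).
- Stated total: 120, as 60 + 60 (Abstract; Sample size).
- Stated precision: ±9 points, 95% confidence interval (Sample size).
- Feasibility targets: 60% recruitment, at most 30% attrition (Analysis).

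**Step 1. Reproduce the plan's own figure.** The half-width of a normal-approximation 95% interval for a proportion is 1.96 × √(p(1 − p)/n). It is widest at p = 0.5. With all 120 women pooled and no allowance for clustering, 1.96 × √(0.25/120) = 0.0895, or ±8.9 points. Solving for ±9 gives n = 0.25 × 1.96²/0.09² = 118.6, so 119 women. The stated precision is therefore consistent with 120 women pooled.

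**Step 2. Count the women from the group description.** Per arm: 4 × 20 = 80. Both arms: 2 × 80 = 160. Against the stated figures, 160 − 120 = 40, and 160/120 = 1.33. An equal split of the stated total would give 60/4 = 15 per clinic and arm.

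**Step 3. Precision at the other total.** 1.96 × √(0.25/160) = 0.0775, or ±7.7 points. Both totals meet ±9.

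**Step 4. Could 160 be the number recruited and 120 the number with data?** The loss that links them is 1 − 120/160 = 25%. No 25% figure appears in the article. The only attrition figure, the 30% ceiling, does not reproduce the pair: 160 × 0.7 = 112, and data from 120 would need 120/0.7 = 171.4, which is 172 women at 86 per arm. If 120 is the number recruited, the ceiling leaves 120 × 0.7 = 84.

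**Step 5. Which outcomes does attrition affect?** For retention, attrition and data completeness the denominator is the women enrolled, because a woman who leaves counts as an event. At 30% attrition with 120 enrolled the half-width is 1.96 × √(0.3 × 0.7/120) = 0.082, or ±8.2 points, inside ±9. Only a proportion measured solely among women with follow-up data uses the smaller denominator. At the 30% ceiling and p = 0.5 its half-width would be ±9.3 points (n = 112) or ±10.7 points (n = 84).

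**Step 6. Workload.** At 60% uptake, 120/0.6 = 200 women must be approached, or 160/0.6 = 267.

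**The case against.** The best defence is that 160 is the enrolment and 120 the expected yield. The Sample size section speaks of collecting data from 120, which can sit beside a larger number recruited, and 20 is the only per-clinic group size that the article gives; 15 is an inference from 60/4. This is a plausible account of how the two numbers arose. It is not what the article says: the abstract attaches recruitment itself to 120, no allowance for loss is stated, and the needed 25% is not the article's attrition figure. The defence shows how the text might be reconciled, but does not reconcile it.

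Two stronger readings are tempting, and the document does not support either.

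- **A reader might infer that the ±9-point claim fails once women drop out.** The 30% is a ceiling for judging feasibility and not a planning assumption. The Sample size section names no time point for the data, and baseline is one of the three collection points. The outcomes for which attrition matters most, retention and completeness, keep the enrolled women as denominator. The claim stands at enrolment for both totals.
- **A reader might infer that success in recruitment cannot be judged until the total is settled.** The criteria in the Analysis section are rates: over 50% of clinics, 60% of women, at most 30% attrition. None is a headcount, and each can be judged with either total.

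It is also fair that this is a feasibility study with no efficacy test, so no power calculation depends on the discrepancy.

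**Conclusion.** The contradiction is real: the text describes 160 women in one section and 120 in two others, a gap of 40 women, with no stated link. The count rests only on four clinics, groups of 20 in each condition and separate cohorts, all of which the article states. The figure of 15 per clinic and arm assumes an equal split.

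The consequence is limited to the planned number, the singing-group size and the recruitment workload (about 200 or 267 women to approach at 60% uptake). The precision statement survives under either total, taken as a pooled, worst-case figure without clustering, and the success criteria do not depend on the headcount. This should be fixed, but it does not undermine the design.

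**What to change.** State one recruitment target per clinic and per arm, and use it in the abstract, in both descriptions of group size in the Intervention section, and in the Sample size section. Which number is meant is for the sponsor to say.

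- **If 120 is the number recruited,** the group sizes in the Intervention section need to agree with 60 per arm, and the pooled worst-case precision is ±8.9 points.
- **If 160 is the number recruited,** the abstract needs to say 160, and the pooled worst-case precision at enrolment is ±7.7 points. If 120 is then the number expected with data, the Sample size section should say so and state the 25% loss that links the two. It should also note that at the 30% ceiling the number left would be 112.

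In either case, say which N the precision refers to, and add that outcomes measured only in women with follow-up data will be less precise.

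The cost is rewording in four places. No woman is needed beyond the target already intended.
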